#### *8.8.2. Sleep measures*

Participants will complete the Sleep Disorders Symptom Checklist-25 (SDS-CL-25; Klingman, Jungquist, & Perlis, 2017), which indicates the presence or absence of common sleep disorders and will be used to verify that participants do not have any other sleep disorders, as well as subjective sleepiness (Karolinska Sleepiness Scale (KSS); Åkerstedt & Gillberg, 1990).

Participants will also complete the Mannheim Dream Questionnaire (MADRE; Schredl, 2014), which provides information regarding the frequency, content and emotional tone of dreams, and will be used to investigate whether these measures differ between good and poor sleepers, since individuals with insomnia have been shown to report more dreams of a negative nature than good sleepers.

Participants will also complete the Insomnia Severity Index (ISI; Bastien et al., 2001), which will be modified in order to assess insomnia severity during the preceding week, rather than assessing insomnia severity during the preceding month, as in the original measure.

#### *8.8.3. Psychological measures*

As general screening measures of subjective anxiety and depression, which are closely associated with insomnia, participants will complete the 7-item Generalised Anxiety Disorder Questionnaire (GAD-7; Spitzer, Kroenke, Williams, & Lowe, 2006) and 9-item Patient Health Questionnaire (PHQ-9; Kroenke, Spitzer, & Williams, 2001). The Perceived Stress Scale (PSS; Cohen, Kamarck, & Mermelstein, 1983), will be used to provide a subjective measure of stress throughout the study.

#### *8.8.4. COVID-19 infection susceptibility and distress measures*

In order to indicate how distressing the ongoing COVID-19 pandemic is considered to be, and to assess beliefs regarding infection susceptibility, and emotional discomfort in contexts which might imply an increased infection potential, participants will complete the Impact of Event Scale-Revised (Weiss, 2007) and Perceived Vulnerability to Disease questionnaire (Duncan, Schaller, & Park, 2009).

#### *8.8.5. Sleep diaries and daily state-trait anxiety*

Participants will complete the Consensus Sleep diary (CSD-M; Carney et al., 2012). This allows measures of sleep continuity (e.g. time in bed, total sleep time) to be derived, as well as measures of sleep quality. Participants will also complete the six-item version of the state scale of the Spielberger State-Trait Anxiety Inventory (STAI; Marteau & Bekker, 1992).

### **8.9. Procedure**

The entire study will be conducted online, and will be delivered using Qualtrics. The full list of assessments to be completed at each time point is included in Table 1.

The end of study will be defined as the final follow-up time point (i.e. 3 months follow-up), or the final study measure completed, should the participant drop out of the study before this point.

Table 1: list of study assessments to be completed at each time point

| Measure                                               | Baseline | Pre-intervention | Post-intervention | One week follow-up | 1 Month follow-up | 3 Month follow-up |
|-------------------------------------------------------|----------|------------------|-------------------|--------------------|-------------------|-------------------|
| Demographic and physical/psychiatric health questions | X        |                  |                   |                    |                   |                   |
| SDS-CL-25                                             | X        |                  |                   |                    |                   |                   |
| KSS                                                   | X        | X                | X                 | X                  | X                 | X                 |
| MADRE                                                 | X        |                  |                   |                    | X                 | X                 |
| GAD-7                                                 | X        | X                |                   | X                  | X                 | X                 |
| PHQ-9                                                 | X        | X                |                   | X                  | X                 | X                 |
| PSS                                                   | X        | X                |                   | X                  | X                 | X                 |
| SF-36                                                 | X        |                  |                   |                    | X                 | X                 |
| Impact of Event Scale-R                               | X        |                  |                   |                    |                   |                   |
| Perceived Vulnerability to Disease                    | X        |                  |                   |                    |                   |                   |
| ISI                                                   | X        | X                |                   | X                  | X                 | X                 |
| CSD-M                                                 |          | X                | X                 |                    |                   |                   |
| STAI                                                  |          | X                | X                 |                    |                   |                   |

#### *8.9.1. Baseline*

After providing informed consent (online), good and poor sleeper participants will provide demographic information (e.g. age, sex), health and occupational information as described earlier. Participants will then complete the SDS-CL-25, KSS, MADRE, GAD-7, PHQ-9, PSS, SF-36, Impact of Event Scale-R, Perceived Vulnerability to Disease questionnaire and ISI. It is expected that the completion of baseline measures will take a maximum of 45 minutes.

Randomisation will also take place at this point. Good sleepers will be randomised to the intervention or no intervention group. Poor sleepers will be randomised to the intervention or wait-list control group.

#### *8.9.2. Sleep monitoring period*

Participants will then be e-mailed a link in order to complete a one-week period of sleep monitoring, which will be completed online. During this period, participants will complete subjective sleep diaries (CSD-M), subjective state-trait anxiety levels (STAI) and subjective sleepiness levels (KSS), approximately 30 minutes after awakening, by logging on to online survey software (Qualtrics) using a mobile phone or suitable internet-enabled device such as a laptop. It is expected that this will take participants approximately five to ten minutes per day to complete.

#### *8.9.3. Intervention*

Poor sleepers will receive the intervention after the one-week baseline period. Poor sleepers who are wait-list controls will receive the intervention after a delay of one month (28 days), and will extend their monitoring period accordingly, with extra ISI, GAD-7, PHQ-9 and PSS measures to be completed on Day 28 (Figure 2).

Participants will repeat the ISI, GAD-7, PHQ-9 and PSS immediately prior to receiving the intervention.

Good sleepers, who will receive the intervention, will do so at the same time as poor sleepers (Figure 2). Good sleepers who do not receive the intervention will follow an identical timeline to the poor sleepers who do receive the intervention (Figure 2).

Assessments will be modified at Day 8 (or the equivalent time point where appropriate) to only ask about the previous week.

#### *8.9.4. Post-intervention*

Following the intervention, all participants will complete daily CSD-M, KSS and STAI measures for one week. Good sleepers who do not receive the intervention will also complete daily CSD-M, KSS and STAI measures.

#### *8.9.5. Follow-up periods*

At one week follow-up (i.e. one week after the intervention), or an equivalent time point for good sleeper participants who do not receive the intervention, participants will complete the KSS, GAD-7, PHQ-9 and ISI. At one month and three months follow-up, participants will complete the KSS, GAD-7, PHQ-9, SF-36, MADRE and ISI. Participants will receive a debrief (Appendix 4) at the end of the study.

Assessments will be modified at follow-up points to only ask about the previous week, with the exception of the SF-36, which will not be modified.

#### **8.10. Participant Timeline**

A detailed participant timeline, with the end of study definition for each participant group, is included in Figure 2.

[figure not shown]

Figure 2: participant timeline

### **8.11. Randomisation & Sequence Generation**

This study will operate as a cluster randomised controlled trial. Good sleepers will be randomised into an intervention or a no-intervention group, with a 1:1 allocation. Poor sleepers will be randomised into an intervention or wait-list control group, with a 1:1 allocation. Randomisation will be conducted automatically using Qualtrics study software, where block sizes will be equal and randomisation will be computer-generated.

Concealment will be assured, as Qualtrics will automatically allocate participants to the appropriate conditions after study entry, and will automatically direct participants to the appropriate online section of the study. Therefore, members of the study team will be unable to determine which arm good sleepers have been allocated to until after study entry. As the allocation sequence will be automatically generated by Qualtrics, randomisation will be conducted without any influence by any member of the study team.

All participants who give consent and fulfil the inclusion criteria will be randomised after the completion of baseline assessments. Due to the nature of the intervention, participants cannot be blinded to the study condition as they will be aware which condition they have been allocated to. For this reason, participants will be allocated a numeric group identification code in the study dataset to denote group allocation (1= good sleeper (no intervention); 2 = good sleeper (intervention); 3 = poor sleeper (wait-list control); 4 = poor sleeper. This is appropriate given the trial design.

The member of the research team who will be conducting the statistical analysis will be blinded to the study condition until the termination of the study. Any routine data monitoring will be undertaken by a member of the research team who will not be responsible for conducting the statistical analysis.

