| Key inclusion and exclusion criteria          | 
Ages eligible for study: ≥18 years
 Sexes eligible for study: both
 Accepts healthy volunteers: yes
 Inclusion criteria:
 
 
Self-reported poor sleepers must meet DSM-5 criteria for acute insomnia.
 
Participants must have an adequate level of English comprehension.
 
 
Exclusion criteria: Individuals with reported chronic sleep disturbances, and those who are currently seeking treatment for their insomnia, and individuals with a self-history of head injuries, a self-reported diagnosis of schizophrenia, epilepsy or personality disorder.
 |
| Study type                                    | 
Study type: interventional
 Allocation: randomised
 Intervention model:
 Masking: single-blind (outcomes assessor)
 Primary purpose: treatment
                                                                                                                                                                                                                                                                                                                                                                                                                                                                     |
| Date of first enrolment                       | TBC (expected first enrolment August 2020)                                                                                                                                                                                                                                                                                                                                                                                                                                                                                                                                                                                                                                   |

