## **8.5. Outcomes**

### *8.5.1. Primary Outcome Measures*

The primary outcome measures will be insomnia severity, as measured using the Insomnia Severity Index (Bastien, Vallières, & Morin, 2001), assessed prior to the intervention and one week, one month and three months post-intervention, relative to baseline.

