## **9. Data Management**

All study data will be electronic and will be obtained from data directly input from the participant. Participant informed consent will be provided electronically. All CRFs and

documentation will be electronic. Paper copies of data or forms will not be held unless they are required in exceptional circumstances (e.g. if CRFs are required by the sponsor); paper copies of documentation will be retained securely in line with standard Northumbria University guidelines.

The online component of the study, and resulting dataset, will be extensively tested prior to the first participant enrolment, to ensure that all methods of data entry are reliable.

The full dataset will be checked and verified for integrity at the end of the study by the principal investigator, and/or other members of the study team. The dataset will also be checked to verify the integrity and quality of data at regular intervals. Any necessary changes to the dataset will be fully documented using a written log.

Anonymised data, and relevant documentation/CRFs will be stored on secure, password-protected computer storage accessible only by the research team. Data will be stored in line with standard university retention guidelines, and will be backed up regularly by Northumbria University IT Services.

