### 11.3. Expected adverse reactions

Expected AEs are summarised below. All AEs are expected to be common and well-understood consequences of study participation.

| Procedure                       | Adverse event                          |
|---------------------------------|----------------------------------------|
| Study questionnaires     | Low levels of psychological discomfort |
| Study sleep intervention | Heightened sensitivity to poor sleep   |

As the intervention will be self-administered, participants will be entirely free to discontinue treatment.

For the purposes of this study, any AEs which the investigators are notified of during the study (i.e. from Day 0 to the final study measure) will be recorded. All AEs will be categorised as to expectedness, relatedness and severity.

Serious AEs exclude any pre-planned hospitalisations (e.g. elective surgery) not associated with clinical deterioration; routine treatment or monitoring of the studied indication which is not associated with clinical deterioration; elective or scheduled treatment for pre-existing conditions that did not worsen during the study; serious AEs exclude changes in insomnia severity or sleep, which are already documented within the study.

All AEs will be reported. Any questions concerning AE reporting will be directed to the principal investigator.

*AEs*: all non-serious AEs will be reported using electronic CRFs and sent to the principal investigator as soon as possible. The severity of AEs will be graded on a three-point scale (mild, moderate or severe). The relation (causality) and seriousness of the AE will be assessed by the principal investigator.

*SAEs*: all SAEs will be reported to the principal investigator within 24 hours of the research team learning of its occurrence. The initial SAE report can be made by telephone or e-mail to the principal investigator. In the case of incomplete information at the time of initial reporting, all appropriate information should be provided as follow-up as soon as this becomes available. Relationship of the SAE to study procedures will be assessed by the principal investigator, as should the expected or unexpected nature of the AE. The sponsor does not need to be informed of SAEs.

Evidence of SAEs will trigger a study monitoring meeting, involving the entire research team, to clarify if the trial will need to be discontinued on the basis of these events. The research

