team will have access to all data accrued to that point and will have the power to terminate the trial early.

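### The registered outcome-assessor masking has nobody to apply to, and the analyst's blind is only role separation: the group code conceals nothing once data are released, and the blind can end early

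*Combined protocol and SAP*

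**What the plan says.** The registration table (section 1) gives the masking as "single-blind (outcomes assessor". Section 8.11 concedes that "participants cannot be blinded to the study condition as they will be aware which condition they have been allocated to" and, giving that as the reason, introduces a group code: "participants will be allocated a numeric group identification code in the study dataset to denote group allocation (1= good sleeper (no intervention", continuing "2 = good sleeper (intervention); 3 = poor sleeper (wait-list control); 4 = poor sleeper". The same section says that whoever does the statistical analysis stays blind until the study terminates, and that routine monitoring falls to a different team member.

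On the source of the data, section 9 states: "All study data will be electronic and will be obtained from data directly input from the participant". Section 8.5.1 states: "The primary outcome measures will be insomnia severity, as measured using the Insomnia Severity Index". The secondary outcomes in section 8.5.2 are the GAD-7, the PHQ-9 and sleep-diary measures.

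On the analyst's access, section 10 excludes the analyst from data checking, and section 16 releases the full dataset to the analyst only at study end. Section 10 also permits the analysis at either of two times: the end of the study period, or the point at which the recruitment target is reached. Section 11.3 states: "Evidence of SAEs will trigger a study monitoring meeting, involving the entire research team". It adds that the research "team will have access to all data accrued to that point and will have the power to terminate the trial early".

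**The concern.** The masking entry tells a reader that someone who did not know the allocation assessed the outcome. That assurance matters most where it is hardest to give: a subjective primary outcome, an intervention that cannot be disguised, and a wait-list comparator. If no such assessor exists, the entry credits the trial with a protection that it lacks.

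The other protection on offer is the analyst's blind. It matters here because section 10 fixes the primary model (a 4 x 5 mixed ANOVA) but leaves open the post hoc tests that follow a significant interaction, with no contrasts and no multiplicity method named for the primary outcome. If the arms can be read from the dataset, those choices would be made by someone who can see which group is which.

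**Working it through.** No figure in the plan depends on masking, so the check sets the statements side by side.

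1. **Who assesses the outcomes?** Section 9 makes the participant the source of all data. The ISI, GAD-7, PHQ-9 and diary are all completed by the participant (sections 8.5.1, 8.5.2 and 8.9). Section 8.11 says that participants know their condition. The only assessor of any listed outcome is therefore an unblinded participant, and the entry in section 1 describes nobody in the trial.

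2. **What does the group code conceal?** Section 8.11 places the code in the study dataset and decodes 1, 2, 3 and 4, which is four of four. Section 16 gives the analyst that dataset in full. Section 8.12 describes breaking the blind as a matter of opening the stored dataset. Once the analyst has the file, the code identifies every participant's arm.

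3. **What protects the analyst before release?** Sections 8.11, 10 and 16 together separate roles: another person monitors, the analyst does not check data, and access comes at the end. While the analyst holds no data, the printed key reveals no participant's arm.

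4. **Can that protection end early?** There are two routes.
   - *Serious adverse event meeting.* Section 11.3 calls in the whole research team and opens all accrued data. Section 10 describes the analyst as a member of the team, and no exception is made.
   - *Analysis when the recruitment target is met.* Read literally, this comes before the last recruits finish. An immediate-intervention poor sleeper recruited last still has one week of monitoring plus three months of follow-up. A wait-list participant has at least 28 days plus three months, or 28 + 7 = 35 days plus three months if the delay follows the monitoring week.

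5. **Would neutral labels be enough?** Not alone. Wait-list participants have a 28-day delay, longer monitoring and extra Day 28 questionnaires (section 8.9.3). Leaflet viewing or download is recorded (section 8.4), and the good-sleeper no-intervention arm should have no such record. Baseline ISI will largely separate good from poor sleepers, so relabelling can only help within each sleeper stratum.

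**The case against.** The strongest reply is that the protocol promises less than a critic might suppose. It claims analyst blinding only up to study termination, and it withholds the data until then. A reader might infer from the printed key that the trial has no blinding of any kind, or that the analyst is unblinded simply by reading the protocol. The documents support neither inference: a key without a dataset identifies nobody, and sections 8.11, 10 and 16 keep the dataset away from the analyst during conduct. This part of the reply stands in full.

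It is also fair to say that participant unblinding is openly disclosed in section 8.11 and cannot be avoided with a self-help leaflet. Relabelling the masking will not reduce reporting bias. That stands too, but it does not rescue the entry in section 1, which claims something different.

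On early loss of the blind, the meeting arises only if a serious adverse event occurs, in a trial that section 12 regards as very low risk, and section 8.12 restricts disclosure of a broken code to other study personnel. A sensible team may also intend to complete follow-up before analysing. These points make early unblinding a contingency rather than a routine event. They do not remove the conflict, because section 11.3 makes no exception for the analyst and section 10 does not require follow-up to be finished.

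Finally, unspecified post hoc tests could be cured by naming them, whoever is blinded. That is true, and it is part of the fix.

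**Conclusion.** The concern holds in a limited form. The registered outcome-assessor masking is a property that the design does not have. Role separation does protect the analyst during conduct, but the group code adds no concealment once the dataset is released, and the promised blind can end before study termination by two routes.

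In size, none of the listed primary or secondary outcomes is assessed by a blinded person, and all four codes are decoded. How far self-report by unblinded participants, or an analyst who can read the arms, would shift the ISI result cannot be derived from the documents, and no bias figure should be inferred. No outcome, sample size or planned primary model needs to change.

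The conclusion assumes that the released dataset carries the codes as section 8.11 describes, that the analyst counts as part of the research team in section 11.3, and that the recruitment-target trigger in section 10 means what it literally says. If the last two are not intended, a sentence each would settle them; the masking entry and the printed key would still need correcting.

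**What to change.** - **Masking statement.** Describe the trial in section 1 as open-label with participant-reported outcomes, with the analyst separated from the data during conduct. State in the conclusions that the ISI comparison with wait-list rests on unblinded self-report.
- **Codes.** Replace codes 1 to 4 with neutral labels assigned at random within each sleeper stratum. Have the existing data-monitoring member (section 8.11) hold the key.
- **Analysis file and code.** Finalise the primary model and the post hoc contrasts in code before the key is released. Use a file limited to the five time points common to all groups, without leaflet-access logs, the extra Day 28 records or the extended-monitoring records. State which wait-list record serves as the pre-intervention value, unless Figure 2 already does so.
- **Access and timing.** Exempt the analyst from group-level data at serious adverse event meetings, and start the analysis only after follow-up ends.

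The cost is some rewording, the recoding of one variable and the preparation of a restricted file. No extra staff are needed, because a separate monitoring member already exists. There are two downsides. The stated masking becomes less favourable. Analyst blinding also stays partial, because outcome patterns or the wait-list schedule may still suggest the arms, particularly among poor sleepers, where the main comparison lies.
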